# Study protocol of the DUtch PARkinson Cohort (DUPARC): a prospective, observational study of de novo Parkinson’s disease patients for the identification and validation of biomarkers for Parkinson’s disease subtypes, progression and pathophysiology

**DOI:** 10.1186/s12883-020-01811-3

**Published:** 2020-06-13

**Keywords:** Parkinson disease, Neurodegenerative diseases, Observational study, Longitudinal studies, Biomarkers, Neuropsychology, Cognition, Gastrointestinal microbiome, Microbiota, Ophthalmology

## Abstract

**Background:**

Parkinson’s Disease (PD) is a heterogeneous, progressive neurodegenerative disorder which is characterized by a variety of motor and non-motor symptoms. To date, no disease modifying treatment for PD exists. Here, the study protocol of the Dutch Parkinson Cohort (DUPARC) is described. DUPARC is a longitudinal cohort study aimed at deeply phenotyping de novo PD patients who are treatment-naïve at baseline, to discover and validate biomarkers for PD progression, subtypes and pathophysiology.

**Methods/design:**

DUPARC is a prospective cohort study in which 150 de novo PD subjects will be recruited through a collaborative network of PD treating neurologists in the northern part of the Netherlands (Parkinson Platform Northern Netherlands, PPNN). Participants will receive follow-up assessments after 1 year and 3 years, with the intention of an extended follow-up with 3 year intervals. Subjects are extensively characterized to primarily assess objectives within three major domains of PD: cognition, gastrointestinal function and vision. This includes brain magnetic resonance imaging (MRI); brain cholinergic PET-imaging with fluoroethoxybenzovesamicol (FEOBV-PET); brain dopaminergic PET-imaging with fluorodopa (FDOPA-PET); detailed neuropsychological assessments, covering all cognitive domains; gut microbiome composition; intestinal wall permeability; optical coherence tomography (OCT); genotyping; motor and non-motor symptoms; overall clinical status and lifestyle factors, including a dietary assessment; storage of blood and feces for additional analyses of inflammation and metabolic parameters. Since the start of the inclusion, at the end of 2017, over 100 PD subjects with a confirmed dopaminergic deficit on FDOPA-PET have been included.

**Discussion:**

DUPARC is the first study to combine data within, but not limited to, the non-motor domains of cognition, gastrointestinal function and vision in PD subjects over time. As a de novo PD cohort, with treatment naïve subjects at baseline, DUPARC provides a unique opportunity for biomarker discovery and validation without the possible confounding influences of dopaminergic medication.

**Trial registration:**

NCT04180865; registered retrospectively, November 28th 2019.

## Background

Parkinson’s disease (PD) is the second most prevalent neurodegenerative disorder, affecting up to 1 in 100 adults over the age of 60 [1]. Despite its large societal impact, the cause of PD remains elusive and only symptomatic treatments exists that mainly targets the motor symptomatology. In addition, the clinical diagnosis of PD poses a clear diagnostic challenge and is rejected in 20% of the cases [2, 3]. Though PD is clinically defined by motor symptoms resulting from dopaminergic neurodegeneration in the substantia nigra, non-motor symptoms are present in the majority of cases and often precede the motor symptoms by years [4]. The constellation of both motor and non-motor symptoms greatly differs between PD subjects, making PD a heterogeneous disorder in which different clinical subtypes might represent different etiologies [5, 6].

To advance our understanding of PD pathophysiology and move towards disease modifying treatments, it is essential to investigate PD as broad as possible, taking into account its large clinical heterogeneity. For this purpose, extensive clinical characterization and biomarker assessments are required for adequate classification of PD subtypes and associated prognostic and pathophysiological markers. Ideally, studies designed to discover and validate biomarkers in PD should only include treatment-naïve PD subjects at baseline, to avoid the possible confounding effect of dopaminergic medication. However, such study cohorts are sparsely available.

This paper describes the study protocol of the DUtch PARkinson Cohort (DUPARC), a single-center, prospective, longitudinal, observational, cohort study at the University Medical Center Groningen (UMCG) of de novo PD subjects, who are treatment-naïve at baseline. PD participants are extensively characterized with the aim to discover and validate biomarkers for PD subtypes, progression and pathophysiology. Though the endpoints assessed in the DUPARC study allow for subject characterization across a wide variety of domains, DUPARC focuses on three domains in particular, representing the interests and expertise of our research group: (1) cognition, (2) gastrointestinal function and (3) vision.

### Cognition

Cognitive dysfunction is a common non-motor symptom in PD that greatly influences the quality of life of patients. Mild cognitive impairment (PD-MCI) is already present in 25–30% of newly diagnosed patients and is considered an important risk factor for the development of PD dementia [7, 8]. The cognitive profile in PD is highly heterogeneous, with multiple cognitive domains affected.

The underlying pathology of cognitive impairment in PD is complex and includes the degeneration of multiple neurotransmitter systems, of which the cholinergic system is thought to be of particular importance [9–11]. In vivo cholinergic imaging studies revealed cholinergic deficits in PD patients compared to control subjects, with the cholinergic loss being even more pronounced in PD patients with dementia, suggesting a direct relationship between cholinergic denervation and cognitive decline in PD [12–14]. However, these findings are based on indirect Positron Emission Tomography (PET) imaging with a tracer binding to acetylcholinesterase. Although acetylcholinesterase is considered to be a reliable target for cholinergic imaging, it is located both on pre- and postsynaptic membranes, and also binds postsynaptically on non-cholinergic neurons [15, 16]. Recently, the selective PET tracer [^18^F]Fluoroethoxybenzovesamicol (FEOBV) was introduced and validated [17, 18]. This tracer binds presynaptically to the vesicular acetylcholine transporter and is a more sensitive and regional cholinergic marker compared to the cholinesterase binding tracers [17, 18].

Combining selective dopaminergic and cholinergic imaging with detailed neuropsychological assessment in a longitudinal cohort of de novo, treatment-naïve PD patients, provides the opportunity to explore the exact role of the cholinergic system in specific cognitive domains, to identify sensitive biomarkers of cognitive decline, and explore future therapeutic targets. We hypothesize that (1) in newly diagnosed, treatment-naïve PD patients, a significant proportion of patients will show cognitive impairment related to regional cortical and subcortical cholinergic denervation; (2) baseline regional cholinergic denervation will be a predictor of cognitive decline in PD over time.

### Gastrointestinal function

Gastrointestinal dysfunction, in particular constipation, is one of the earliest manifestations of PD and can occur up to 20 years before diagnosis [19]. In concordance with the symptomatology, alpha synuclein deposition in Lewy bodies and neurites, the pathological hallmark of PD, are also found in the Enteric Nervous System (ENS) of PD cases [20, 21]. The alpha synucleinopathy is believed to spread in a prion-like manner via the vagal nerve to the brain [22]. Moreover, intestinal inflammation and an increased intestinal wall permeability are found in PD [23]. Possible determinants of the enteric pathology in PD include gut microbiota, which were found to modulate the synucleinopathy, neuroinflammation and motor symptomatology in a rodent PD model [24].

Recently, 16 independent studies have shown that the gut microbiota composition of PD patients is significantly different from healthy age-matched controls (HC) [25]. Interestingly, the gut microbiome changes in PD do not match those in idiopathic constipation, despite the high prevalence of constipation in PD [26]. So far, published studies on gut microbiota composition in PD almost exclusively included dopamine-suppleted PD patients, which is a significant confounder. Moreover, subtype analyses within PD have been limited, in which PD subjects with autonomic dysfunction, indicative of a possible gut-first subtype, might be of particular interest [27]. Therefore, to advance the development of gut microbiota composition as a biomarker or possible therapeutic target in PD, it is a requirement to establish the gut microbiota composition of extensively characterized treatment-naïve PD patients.

We hypothesize that (1) gut microbiome composition of treatment-naïve de novo PD subjects is different from HC; (2) dopaminergic medication drives differential abundance of gut microbial taxa independent of PD progression; (3) PD subjects with autonomic dysfunction, indicative of a gut-first subtype, will show distinct gut microbial signatures compared to other PD subjects; (4) the gut microbiome changes in (constipated) PD subjects will be different from the changes in idiopathic constipation subjects; (5) the intestinal wall permeability will be increased already in de novo PD subjects with concomitant signs of intestinal inflammation.

### Vision

PD presents with a broad range of visual system dysfunctions, including visual hallucinations and defects in color vision, contrast sensitivity and visual fields [28–32]. Along with visual symptoms, thinning of the retinal nerve fiber layer can be assessed by optical coherence tomography (OCT) and is observed in PD, including thinning of the inner-plexiform and the ganglion cell layer [33]. The pattern of retinal thinning and the peripheral visual defects in PD bear resemblance with glaucoma, a disorder with a pathophysiological and epidemiological link with PD [34, 35]. Though retinal thinning has been suggested as possible biomarker for PD diagnosis, severity and progression [32, 36], our understanding of the visual system in PD, and the possible link with pathologies such as glaucoma, is still limited.

Two studies have been published investigating the retina in de novo treatment-naive patients with OCT [37, 38], and reported statistically significant thinning of the retinal nerve fiber layer and macular ganglion cell-inner plexiform layer. In treated PD subjects, it has been shown that dopaminergic treatment and other interventions commonly applied in PD, such as deep brain stimulation, can alleviate some of the visual symptoms present in PD, but are also able to induce or worsen visual symptoms [30]. However, there is a lack of longitudinal studies incorporating the effect of dopaminergic treatment in PD. In order to understand the effects of PD on visual function and retinal structure, including the seemingly contradictory effects of PD medication, there is a need for an in-depth ophthalmological assessment in a longitudinal PD cohort, with data collection before and after treatment initiation.

We hypothesize that (1) de novo PD patients will show a specific pattern of retinal thinning, in particular affecting the inner plexiform layer; (2) the retinal thinning pattern of PD will be different from glaucoma, with retinal changes focusing on the inner plexiform layer in PD, contrary to the ganglion cell layer in glaucoma; (3) dopaminergic medication will increase the thickness of retinal cell layers, especially the inner plexiform layer; (4) the severity of retinal thinning will be a predictor of PD disease progression.

## Methods/design

### Study design

The DUPARC study is a single center, prospective, observational study of 150 de novo PD patients who are treatment naïve at baseline with follow-up after 1 year and 3 years, with the intention of an extended follow-up with three-year intervals. DUPARC is designed to assess 16 specific objectives with a focus on the domains of cognition, gastrointestinal function and vision, with the overarching aim to discover and validate biomarkers for PD subtypes, progression and pathophysiology (Table 1).

**Table 1 Tab1:** Objectives of the DUPARC cohort study

**Overall aim**	
To discover and validate biomarkers for Parkinson’s disease (PD) subtypes, progression and pathophysiology.	
**General**	
1.	To combine clinical assessment of both motor and non-motor symptoms with outcome measures across multiple domains, including neuropsychology, gastroenterology and ophthalmology.
**Cognition**	
2.	To establish the relationship between cognitive impairment and cholinergic innervation in treatment-naïve PD patients.
3.	To determine the relationship between cognitive impairment and dopaminergic innervation in treatment-naïve PD patients.
4.	To investigate the progression of the cognitive profile of de novo PD patients and determine the incidence of PD associated mild cognitive impairment over time.
5.	To identify potential biomarkers of longitudinal cognitive decline within the brain neurotransmitter system.
6.	To identify potential biomarkers of longitudinal cognitive decline within the brain functional connectivity and white matter tracts using functional MRI and diffusion tensor imaging.
**Gastrointestinal function**	
7.	To establish the gut microbiome composition of treatment-naïve PD subjects compared to age- and sex-matched control subjects.
8.	To determine the possible influence of dopaminergic medication on gut microbiome composition in PD after 1 year of dopaminergic medication use.
9.	To determine the specificity of gut microbiome changes for PD diagnosis by additionally correcting for possible confounders other than dopaminergic medication, eg. dietary habits, presence and severity of constipation, non-dopaminergic medication, disease history.
10.	To identify potential biomarkers of PD within the gut microbiome, ranging in complexity from the identification of key microbes, suitable for rapid quantification, to complex microbial fingerprints. Potential biomarkers of PD should be further validated for their specificity compared to other neurological and neurodegenerative disorders, as well as their robustness in other PD microbiome studies.
11.	To correlate changes in gut microbiome composition in PD to specific PD subtypes in terms of clinical presentation, rate of progression, genetic risk profile and/or imaging parameters.
12.	To investigate the gut permeability of treatment-naïve PD subjects through the assessment of fecal and serum markers, as well as a urinary sugar excretion test.

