#### Recruitment strategy

Participants are recruited via Parkinson Platform Northern Netherlands (PPNN), a collaborative network of PD treating neurologists in 13 medical centers in the northern part of the Netherlands. PPNN serves a total of approximately 5000 PD patients, with an incidence of 400 newly diagnosed PD patient within this network. Treatment-naïve de novo PD subjects who are willing to participate are referred to the University Medical Center Groningen (UMCG) to assess the in- and exclusion criteria. After inclusion and completion of the baseline assessments, patients return to their treating neurologist to continue care as usual, including the start with dopaminergic treatment.

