#### Control cohorts

Though the complete DUPARC protocol solely concerns de novo PD subjects, there is ample opportunity to interpret the assessed endpoints relative to appropriate control cohorts. Primarily, age- and sex-matched control subjects are recruited separately to ensure identical assessment techniques for the neuropsychological, gastroenterological and ophthalmological assessments, representing the three main domains of the protocol. In addition, appropriate control subjects for the ophthalmological assessments, including HC and over 1000 glaucoma patients, are available under a different IRB-protocol in the UMCG. These all received the ophthalmological assessments, including retinal imaging, according to the UMCG standard operating procedures, using the same OCT machine, during overlapping periods, to ensure maximal compatibility with the DUPARC data. Complementary, the gut microbiome and genetic assessments will be compared to control subjects from LifeLines, a three generation, population-based cohort study concerning 167.000 participants from the same geographical area in the northern part of the Netherlands [39]. Of these participants, biomaterials such as fecal samples and blood samples have been collected in two large subcohorts (*n* = 9.000 and *n* = 1.100) [40, 41]. In addition, 38.000 LifeLines participants, of a total of 53.000 participants of whom genotype data is available, have received the same genome-wide genetic assessment using the Illumina GSA-MD chip. Genotype information will eventually become available for all 167.000 LifeLines participants. To ensure compatibility, the LifeLines standard operating procedures for the gut microbiome and genetic analyses are also used in DUPARC. Biomaterial from selected LifeLines participants can be reanalyzed to assess possible batch effects. Moreover, stool frequency and consistency has been assessed using the same stool diary in DUPARC and LifeLines, allowing for the identification of LifeLines subjects with idiopathic constipation. Lastly, a large proportion of endpoints, including the neuropsychological assessments, will be assessed using norm-rated tools that depict the performance of the patient as a percentile corrected for relevant demographics, such as age and level of education.

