**Fig. 1 Fig1:**
[figure not shown]
Baseline recruitment and assessments from Q4 2017 to Q3 2020 of treatment-naïve de novo PD subjects through the collaborative network of PD treating neurologists Parkinson Platform Northern Netherlands (PPNN). 1. Study procedures start at home with 1a. the collection of a saliva sample for genetic screening; 1b. Assessments of gastrointestinal function and stool sample collection; 1c. questionnaire assessments. 2. Participants visit the University Medical Center Groningen (UMCG) on 2 days for 2a. a complete cognitive assessment; 2b. imaging; 2c. ophthalmological assessments; 2d. clinical assessments. * In a subset of participants, intestinal wall permeability will also be assessed using blood samples and a urinary excretion test. ** Hyposmia is also assessed using the Sniffin’ sticks. Source clipart: clipart-library.com

Participants will receive follow-up assessments after 1 and 3 years, with the intention of an extended follow-up with three-year intervals. After 1 year, participants are visited at home for a repeated gastroenterological, clinical and questionnaire assessment. During the three-year follow-ups the complete baseline assessments are repeated with the exception of the genetic and gastrointestinal assessments. All assessed endpoints and the time of assessments are presented in Table 2.

**Table 2 Tab2:** Overview assessments DUPARC

Assessments	Endpoint	Baseline	Follow-up 1 year	Follow-up 3 years

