**Gastrointestinal function**				
16S rRNA gene and metagenomic sequencing	Fecal microbiome composition	X	X	
Stool diary (7 days)	Stool frequency and consistency	X	X	
Dietary diary (3 days)	Nutrient intake	X	X	
Fecal calprotectin	Intestinal wall permeability - inflammation	X		
Fecal alpha1-antitrypsin	Intestinal wall permeability - protein leakage	X		
Serum zonulin^a^	Intestinal wall permeability - mucosal barrier integrity	X		
Urinary sugar excretion test^a^	Intestinal wall permeability	X		
Serum LPS^a^	Intestinal wall permeability - microbial translocation	X		

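### Objective 8 and hypothesis 2 on dopaminergic medication and the gut microbiome claim more than two stool samples one year apart, with an unset treatment start, can show

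*Protocol article*

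**What the plan says.** **The aim.** Table 1 of the protocol article, objective 8: "To determine the possible influence of dopaminergic medication on gut microbiome composition in PD after 1 year of dopaminergic medication use". Hypothesis 2 in the Background (Gastrointestinal function) is stronger: "dopaminergic medication drives differential abundance of gut microbial taxa independent of PD progression".

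**When treatment starts.** Recruitment strategy: after the baseline assessments, "patients return to their treating neurologist to continue care as usual, including the start with dopaminergic treatment". The article fixes no start date and no minimum exposure.

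**When stool is taken.** Study procedures: "After 1 year, participants are visited at home for a repeated gastroenterological, clinical and questionnaire assessment". The three-year visits repeat the baseline programme "with the exception of the genetic and gastrointestinal assessments". Table 2 agrees: the row "16S rRNA gene and metagenomic sequencing" is marked at baseline and 1 year and is empty at 3 years.

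**Who is followed.** Control cohorts opens with "Though the complete DUPARC protocol solely concerns de novo PD subjects". It then describes separately recruited matched controls and LifeLines participants. It mentions neither an untreated PD group nor a second stool sample from controls after one year.

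**The concern.** There are two separate problems.

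1. **Exposure.** The objective counts a year from the start of medication. The visit counts a year from baseline. These are different clocks, and treatment starts after baseline.
2. **Attribution.** Between the two samples every patient becomes a year older and a year further into the disease, and patients start treatment along the way. Diet and laboratory batch may change as well. The average change over that year is the sum of all of these. Calling a change independent of progression needs something that separates drug from time, and no comparison group in the article does so.

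The article itself treats medication as a significant confounder of earlier microbiome studies. Its Discussion says that the cohort can help to separate medication effects from disease effects. A drug claim drawn from the average one-year change would bring that ambiguity back.

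**Working it through.** **The plan's own figures.** None is given for objective 8: Sample size says that power cannot be calculated for metagenomic analyses. The one power figure in the article concerns retinal imaging and reproduces. With effect size 0.45, two-sided alpha 0.05 and power 0.80, a two-sample t-test needs 78.5, rounded up to 79 per group. The 180 recruited less 30 losses gives the 150 used below.

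**Step 1: exposure at the second sample.** Take the visit at 12 months from baseline. A patient who starts m months after baseline has 12 − m months of exposure, and a non-starter has zero. Start dates are not given, so as an assumption let m be uniform on 0 to k months. The mean exposure is 12 − k/2:

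- k = 3: 10.5 months
- k = 6: 9 months
- k = 12: 6 months

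**Step 2: what the average change contains.** For one taxon, write change = a + b × exposure + error, where a is everything that a year does without the drug. If exposure is coded yes/no and all 150 patients are treated, the columns for a and b are identical (rank 1 of 2), and b cannot be estimated. Information on b comes only from differences in exposure between patients.

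**Step 3: size of the ambiguity (illustration).** Set b = 0 and let a be d SDs of within-person change. A paired t-test at two-sided 0.05 has noncentrality d√150:

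| d (assumed) | d√150 | Rejection rate |
|---|---|---|
| 0.1 | 1.22 | 22.9% |
| 0.2 | 2.45 | 68.2% |
| 0.3 | 3.67 | 95.5% |

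This is one taxon without multiplicity correction. Both the drift and the test are assumptions.

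**Step 4: what variation in exposure can recover.** All figures use N = 150, 80% power, two-sided 0.05, and 1.96 + 0.84 = 2.80.

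*(a) Start date, linear in months, free time term.* The SD of exposure is k/√12. The smallest detectable effect of 12 months on drug, in SDs of change, is 2.80 × 12 / (√150 × SD of exposure):

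| k | SD of exposure (months) | With time term | Without time term |
|---|---|---|---|
| 3 | 0.87 | 3.2 | 0.26 |
| 6 | 1.73 | 1.6 | 0.30 |
| 12 | 3.46 | 0.8 | 0.40 |

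The last column replaces the SD by √(mean² + SD²). The gain in precision comes only from assuming that a = 0.

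*(b) Treated against still untreated at 1 year.* The formula is 2.80 × √(1/n₁ + 1/n₀):

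- 142 treated, 8 untreated: 1.02 SD
- 135 and 15: 0.76 SD
- 120 and 30: 0.57 SD
- 75 and 75: 0.46 SD

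The article does not say how many patients, if any, will be untreated at 1 year.

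**Step 5: can other planned data stand in for a time control?** MDS-UPDRS II and III, the stool diary and the dietary diary are repeated at 1 year. However, the Background says that current treatment acts mainly on motor symptoms, so the 1-year motor score mixes progression with drug response. Both PET scans are done at baseline and 3 years only, so the 1-year stool sample has no matching image of progression. Reanalysing LifeLines material addresses batch, not one year of disease. Objective 9 concerns specificity for the diagnosis and corrects for confounders other than dopaminergic medication.

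**The case against.** The strongest reply is that the article states no before-after test. Statistical analysis says only that methods will suit each objective, and the model may sit in a full protocol or SAP that is not shown. This stands: the rejection rates in step 3 describe a risk, not the planned analysis. It does not remove the point, because no analysis plan can change when stool was taken or add a comparison group.

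Three stronger readings are tempting, and the documents do not support them.

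- **That medication start and dose are not recorded.** A reader might infer this from "All assessed endpoints and the time of assessments are presented in Table 2", since that table has no medication row. But Table 2 lists assessments rather than form fields. Objective 9 plans to correct for non-dopaminergic drugs, which have no row either. Disease history and MDS-UPDRS IV are taken at 1 year, and the microbiome study has its own registration. The data may well be collected.
- **That drug and time cannot be separated at all.** This would hold only if every patient had the same exposure. Differences in start date, dose or treatment status allow a partial analysis. It is weak (step 4) and not randomised, and exposure probably follows severity.
- **That the cohort fails in its purpose.** Its main protection against medication effects is that patients are untreated at baseline. Sample size names the comparison with healthy controls as the main gastrointestinal objective. Objective 8 is one of 16, and the baseline results do not depend on it.

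Objective 8 does speak of a possible influence, which softens it. Hypothesis 2 has no such hedge.

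**Conclusion.** The point holds as a mismatch between what is claimed and what the schedule can show.

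- The second stool sample is not taken after a year on medication. Exposure then is below 12 months for anyone starting after baseline and varies between patients. This follows from the schedule and needs no numerical assumption beyond a visit at about 12 months.
- With two samples, no untreated PD group and no repeat-sampled controls, the design does not support an effect independent of progression. It supports an association at most.
- The numerical size depends on assumptions. The 23%, 68% and 95% rejection rates need the assumed drift and an unstated paired test. The detectable effects of 0.8 to 3.2 SD need uniform start dates and a linear exposure effect.

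This limits what may be concluded from objective 8 and hypothesis 2. It does not reach the other gastrointestinal objectives.

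**What to change.** 1. **Reword objective 8** to the change in microbiome composition one year after baseline, after up to one year on dopaminergic medication.
2. **Reword hypothesis 2** as an association between medication exposure and taxon abundance, and state that the design does not separate it from progression.
3. **Analyse each patient's change against recorded exposure**: time since start and cumulative dose, zero for non-starters, with a free time term. Adjust for baseline abundance, baseline severity, baseline diet and baseline stool pattern.
4. **Keep adjustment for change** in MDS-UPDRS, stool consistency or laxative use as a sensitivity analysis. Treatment may affect these, so adjusting for them could remove part of a drug effect.
5. **Report the drug effect as exploratory**, with the distribution of exposure at the 1-year visit and the number still untreated.

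The cost is some wording and an analysis specification. If start dates or doses are not already held, they would have to be retrieved. The conclusion becomes weaker and associational, and power is lower than for a simple before-after comparison.
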